### Implementation and process evaluation

A mixed-methods explanatory design will explore the acceptability, feasibility and factors influencing implementation. The evaluation is informed by Proctor *et al*’s Implementation Outcome Framework, the TFA.

#### Patient participants

All trial participants will complete the 8-item TFA questionnaire at each assessment time point. Up to 12 participants will be purposively sampled for qualitative interviews 3–4 weeks postprocedure, conducted face-to-face or remotely by an experienced researcher using a semistructured, iterative guide codeveloped with PPI&E representatives.

#### Practitioner participants

All practitioners performing the procedures will complete online surveys (TFA, Intervention Appropriateness, Feasibility of Intervention Measure, Innovation-Specific Implementation Intentions) within 72 hours postprocedure. Up to 20 practitioners will be purposively sampled for qualitative interviews exploring training, delivery and implementation barriers/facilitators. Interviews will be transcribed and analysed thematically using TFA domains, with participant checking and PPI&E/advisory input to contextualise findings.

### Health economic evaluation

A microcosting analysis will capture intraprocedural costs, including devices, consumables and staff time. Additional NHS and community health service use will be collected over 90 days, alongside EQ-5D-5L for Quality Adjusted Life Years (QALY) estimation. Secondary analyses will include productivity losses. Where appropriate, long-term outcomes will be modelled using a state-transition approach. Sensitivity analyses will assess uncertainty. All analyses will follow National Institute for Health and Care Excellence (NICE) and Consolidated Health Economic Evaluation Reporting Standards guidelines.

### Measurement of costs and outcomes

Health economic analysis includes direct and indirect costs.

### Statistical methods

#### Planned analyses for primary and secondary outcomes

The primary analysis will be performed on an ITT basis, including all randomised participants as allocated. The primary outcome—log SCr at 2, 30 and 90 days postprocedure—will be analysed using a mixed-effects model with participant as a random effect to account for repeated measures over time. The model will adjust for baseline log SCr, stratification and minimisation factors (age, sex, baseline CKD stage and presence of tissue loss).

Secondary outcomes will be analysed using appropriate statistical methods: binary outcomes (eg, AKI incidence, MAKE) will be compared between groups using logistic regression; continuous outcomes (eg, contrast volume, QoL scores) will be analysed using linear regression, or non-parametric tests if data are not normally distributed. Time-to-event data, if applicable, will be analysed using survival analysis methods such as Kaplan-Meier estimates and Cox proportional hazards regression. All analyses will be conducted using validated statistical software according to a prespecified SAP.

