### Outcomes

Outcomes and assessments are based on national and international consultation with AKI experts, our national stakeholder/patient survey, patients’ opinions during our patient involvement work and our previous/ongoing randomised and observational research relating to renal decline in vascular patients.^1^

We plan to evaluate the impact on kidney function postendovascular revascularisation in the RCT arms both in the short term (AKI) and at 90 days (medium term). We will include creatinine measurements at 2, 30 and 90 days, powered to detect a clinically meaningful difference in serum creatinine (SCr) at 90 days. These three SCr measurements will also allow us to compare AKI incidence based on the Kidney Disease Improving Global Outcomes (KDIGO) definition of AKI between groups and calculate/compare the incidence of major adverse kidney events at 90 days (MAKE outcome). This will provide novel information on the clinical value of using the proposed intervention, addressing the relevant evidence gap and leading to adoption of the intervention in the NHS, for the immediate benefit of patients in this high-risk group. We have chosen not to use AKI incidence at 2 days as the primary outcome, as it does not allow us to evaluate medium-term renal injury and would also necessitate recruitment of a prohibitively large sample of patients, without adding clinical information that would aid translation to clinical care.

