### Statistical considerations

#### Sample size calculation

174 patients (87 per group) provide 90% power to detect clinically meaningful differences. Based on our preliminary data (observational AKI study of 2021 patients with PAD/CKD treated in three sites and a pilot study on the use of CO_2_ in PAD procedures),^78 15^,^17^ we expect the SD of log SCr values at 2, 30 and 90 days to be 0.25 log (µmol/L). We assume the correlation of the baseline, 2, 30 and 90-day measures to be 0.67, which is conservative. With these assumptions, a sample size of 156 patients (78 per group) would have a 90% power to detect a mean difference of 0.075 log (µmol/L) in SCr values (effect size of 0.3) at 2, 30 and 90 days postsurgery, between intervention and control groups with an alpha value of 0.05. Allowing for a 10% drop-out, 174 will be recruited. This sample size will also allow us to assess for a 20% reduction in the volume of iodinated contrast used in those having the intervention versus control (median of 70 mL of iodinated contrast used in our published series without CO_2_). In order to ensure the population remained truly per intention-to-treat (ITT) for the primary outcome, multiple imputation will be implemented to deal with missing data in instances where participants are missing any of the SCr values. Values will be predicted using a multivariate normal regression equation with 20 imputations being used.

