#### Data analysis

The LCTU Trial Statistician will be responsible for planning, monitoring and carrying out analyses, supervised by a senior statistician. Statistical analysis will be undertaken according to a prespecified statistical analysis plan (SAP) written prior to database lock and reported following Consolidated Standards of Reporting Trials statements. The baseline characteristics of the participants will be summarised by group. Continuous variables will be summarised using mean and SD, or median and IQR if data do not have a symmetric distribution. Categorical variables will be summarised with counts and percentages. The primary analysis of the primary outcome will be carried out in the ITT population using a mixed effects model with participant as a random effect to account for repeated measures over time. Each participant will contribute up to three repeated outcome measures to the model in addition to the baseline SCr. The model will be adjusted for the stratification and minimisation variables (age, sex, baseline CKD stage and presence of tissue loss). Secondary outcomes will be analysed on a complete case population and reported similarly to the primary outcome using appropriate methodology to compare randomised groups; binary outcomes using logistic regression, continuous outcomes using linear regression or, where not normally distributed, using appropriate non-parametric methods.

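### The primary mixed model as described gives one effect averaged over days 2, 30 and 90, not the 90-day effect the trial says it is powered for; a visit-specific effect needs an arm-by-visit term and a covariance that may differ by visit.

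*Protocol article*

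**What the plan says.** Two sections of the protocol article describe the primary model in nearly the same terms. Under Planned analyses for primary and secondary outcomes, the three log creatinine values "will be analysed using a mixed-effects model with participant as a random effect to account for repeated measures over time", and "The model will adjust for baseline log SCr, stratification and minimisation factors". Under Data analysis, the model is again one "using a mixed effects model with participant as a random effect to account for repeated measures over time", and "Each participant will contribute up to three repeated outcome measures to the model in addition to the baseline SCr". Neither section mentions a visit term, an arm-by-visit term or a residual covariance structure. Both refer to a prespecified SAP, which is not shown.

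On the target, the Outcomes section separates a short-term from a medium-term evaluation and describes the trial as "powered to detect a clinically meaningful difference in serum creatinine (SCr) at 90 days". The Sample size calculation instead aims to "detect a mean difference of 0.075 log (µmol/L) in SCr values (effect size of 0.3) at 2, 30 and 90 days postsurgery". It assumes one SD of 0.25 for all three visits, and "We assume the correlation of the baseline, 2, 30 and 90-day measures to be 0.67, which is conservative". Missing creatinine values are to be filled by multivariate normal multiple imputation with 20 imputations.

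**The concern.** The participant random effect is the only device named for handling the repeated measures. In its plain form, a random intercept with independent residuals of one variance, it implies the same residual variance at every visit and the same correlation between every pair of visits. Day 2 is an acute measurement and day 90 a medium-term one, and a single baseline slope need not leave equal residual spread at both.

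Two things follow. First, without an arm-by-visit term the model produces no 90-day effect, although Outcomes names that time point for power. Second, if the interaction were simply added to the plain model, every visit's contrast would carry a standard error built from the variance pooled over visits. At a visit with above-average residual variance that standard error is too small, and at one with below-average variance it is too large. At stake is whether the 90-day conclusion has its nominal error rate.

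**Working it through.** **Inputs from the document (Sample size calculation).** SD 0.25, correlation 0.67 throughout, difference 0.075, power 90%, alpha 0.05 (taken as two-sided), 78 per arm evaluable, 10% drop-out.

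**1. Reproduce the plan's figure.** For the baseline-adjusted mean of three visits with equal SDs and correlations, the variance factor is (1 + 2 × 0.67)/3 − 0.67² = 0.7800 − 0.4489 = 0.3311. Then n per arm = 2 × (1.960 + 1.282)² × 0.25² × 0.3311 / 0.075² ≈ 77.3, so 78 per arm and 156 in total. 156/0.9 = 173.3, so 174. The stated size is reproduced, and it belongs to the visit average.

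**2. Day 90 alone, same inputs.** The factor is 1 − 0.67² = 0.5511. The standard error at 78 per arm is 0.25 × √0.5511 × √(2/78) = 0.0297. Power is Φ(0.075/0.0297 − 1.96) ≈ 71% (76% at 87 per arm). For 90% power, 129 per arm are needed: 258 evaluable, 287 with 10% drop-out.

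**3. Day-90 contrast from a random-intercept model with arm-by-visit added.** With complete data and one baseline slope b, the residual variance at visit t is R_t = σ_t² − 2b·cov(baseline, t) + b²σ_0². The model's standard error uses the mean of R_t over visits and the true one uses R_90. Hence type I error = 2 × [1 − Φ(1.96 × √(mean R / R_90))].

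Worked example, *assumed* correlations with baseline of 0.80/0.67/0.55 and SD 0.25 throughout:
- b = (0.80 + 0.67 + 0.55)/3 = 0.6733.
- R_2 = 0.02350, R_30 = 0.03444, R_90 = 0.04454; mean 0.03416.
- Model SE = √(2 × 0.03416/78) = 0.0296; true SE = √(2 × 0.04454/78) = 0.0338; ratio 0.88.
- Type I error = 2 × [1 − Φ(1.717)] = 8.6%.

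**4. Range of patterns.** Only the first row uses the document's figures; the rest are assumptions. The last column is from 10,000 simulated null trials with 78 per arm.

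| Pattern, days 2/30/90 | Model SE ÷ true SE, day 90 | Type I error, formula | Simulated |
|---|---|---|---|
| Document: SD 0.25, correlation 0.67 | 1.00 | 5.0% | 5.0% |
| Baseline correlation 0.75/0.67/0.59 | 0.91 | 7% | not run |
| SD 0.25/0.25/0.30, correlation 0.67 | 0.89 | 8.1% | 7.7% |
| Baseline correlation 0.80/0.67/0.55 | 0.88 | 8.6% | 8.4% |
| SD 0.20/0.25/0.30, correlation 0.67 | 0.84 | 10% | not run |
| SD 0.25/0.28/0.32, baseline correlation 0.80/0.67/0.55 | 0.80 | 11.7% | 11.9% |
| SD 0.30/0.27/0.25, correlation 0.67 | 1.10 | 3.2% | 3.3% |
| SD 0.30/0.25/0.22, correlation 0.67 | 1.17 | 2.2% | 2.2% |

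**5. Visit-averaged effect.** With complete data this is an analysis of each participant's mean, and its variance is estimated from those means whatever the within-participant pattern. Model and true standard errors agreed in the six patterns that were simulated (0.0230 for both under the document's figures, 0.0236 for both in the worked example). Simulated type I error was 4.9% to 5.6%, using 1.96 as the cut-off.

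**The case against.** The strongest reply is that the plan contains no faulty contrast. Neither description of the model has an arm-by-visit term, the sample size belongs to the visit average, and for that average the standard error is valid. Residual structure and degrees of freedom are details that an article commonly leaves to the SAP, and nothing in the text rules out a richer covariance. The short-term conclusion may rest on AKI, and part of the 90-day conclusion on major adverse kidney events. Both are binary outcomes planned for logistic regression, which this issue does not touch.

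Most of this stands. A reader might infer that the primary test has an inflated error rate; step 5 shows that it does not for the effect as described. A reader might infer that a day-90 result would be declared significant too often; the document gives no visit-specific variances, and the last two rows of the table reverse the direction. A reader might also infer that missing visits combined with a wrong covariance would bias the average. The plan imputes missing creatinine and adds sensitivity analyses, and if data are not missing at random an unstructured covariance would not remove the bias either.

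What the reply does not answer is the mismatch. Outcomes names day 90 as the powered target, and the model stated in two sections does not deliver a 90-day effect. The obvious extension of that model would give one with a standard error that depends on an untested equality.

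**Conclusion.** The point holds as a mismatch between model and stated target, with a conditional risk to the standard error. As described, the primary model estimates an average over days 2, 30 and 90, validly on complete data or on data imputed under a tenable missing-at-random assumption. It does not estimate the 90-day difference for which Outcomes claims power; on the plan's own inputs a 90-day comparison has about 71% power at 78 per arm.

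If a 90-day effect were taken from a random-intercept model with common residual variance, its type I error would be 5% under the flat assumptions. It would be about 7-12% under the assumed patterns with more spread at day 90, and about 2-3% under those with more spread at day 2. These figures rest on assumed patterns, complete data and a single baseline slope. They do not show that the planned primary test is invalid, or which way a day-90 error would go. The change is worth making because it is cheap and removes the dependence on an unknown pattern.

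**What to change.** Specify the primary model as a repeated-measures mixed model on log creatinine. Use fixed effects for visit, arm-by-visit, baseline log creatinine-by-visit and the minimisation factors, an unstructured within-participant covariance, and Kenward-Roger degrees of freedom. State a fallback covariance structure in case the model does not converge. Fit it to each imputed dataset in the planned multiple imputation and pool the results.

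Report both the visit-averaged and the 90-day contrast from this one model, and state which is primary. If it is the average, the 156/174 stands and the power sentence in Outcomes should be brought into line. If it is day 90, the power statement and sample size need to be revisited.

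The cost is protocol and SAP wording. An unstructured covariance for three visits has six parameters against two for a random intercept, so four more, which about 156 participants support easily. The downside is a small risk of non-convergence, which the stated fallback covers.

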### Interventions

Participants will be randomised to either:

*Control group*: standard iodinated contrast medium used during endovascular PAD revascularisation (standard of care).*Intervention group*: CO_₂_ contrast, delivered via a dedicated injector system (Angiodroid injector) as an alternative to iodine contrast.

All other procedural aspects remain consistent across groups and as per the usual standard of care (pragmatic RCT). Those in the intervention group will be allowed the administration of standard iodine-based intra-arterial contrast if deemed necessary by the operators in order to complete the procedure safely.

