### Secondary outcomes

#### Key secondary outcome

Volume of iodinated contrast medium used during endovascular revascularisation.

The trial is adequately powered to assess both the primary outcome and the key secondary outcome. This will provide clinicians with high-quality definitive evidence and data necessary in order to adopt this intervention into their routine clinical practice.

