### Participant timeline and schedule of events

Participants will be screened and consented up to 15 days prior to the index procedure. Baseline assessments include medical history, demographics, height, weight, baseline SCr and patient-reported outcome measures relating to QoL (using the patient-preferred EQ-5D-5L and SF-36 forms).

Randomisation occurs after consent and baseline measurements, allocating participants 1:1 to iodinated contrast medium or CO_2_ via an automated injector. The index procedure (endovascular revascularisation) will be performed within 15 days of consent.

Follow-up assessments will coincide with routine NHS care at Days 2, 30 and 90 after the procedure. These include SCr measurements, repeat patient-reported outcome measures (Day 90), pain scores (VAS during the index procedure) and healthcare resource use questionnaires (Day 90).

An optional qualitative interview will be offered 3–4 weeks postprocedure to a purposive sample of participants and practitioners to explore intervention acceptability and implementation factors.

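### A normality check on the observed data decides how contrast volume and quality of life are analysed, and neither branch is tied to the 20% contrast target or to the baseline quality-of-life scores

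*Protocol article*

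**What the plan says.** Under Planned analyses for primary and secondary outcomes, the article states that "continuous outcomes (eg, contrast volume, QoL scores) will be analysed using linear regression, or non-parametric tests if data are not normally distributed". The Data analysis section gives the same rule in slightly different words: "continuous outcomes using linear regression or, where not normally distributed, using appropriate non-parametric methods". One section speaks of *tests*, the other of *methods*. Neither gives a criterion for normality, a named fallback or an effect measure.

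The rule covers the key secondary outcome, "Volume of iodinated contrast medium used during endovascular revascularisation", of which the article says: "The trial is adequately powered to assess both the primary outcome and the key secondary outcome". The Sample size calculation section sets the target as a 20% reduction and gives a median of 70 mL without CO2. It gives no SD and no separate power figure for this outcome.

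Quality of life is collected before the procedure as well as at day 90. Baseline assessments include "baseline SCr and patient-reported outcome measures relating to QoL (using the patient-preferred EQ-5D-5L and SF-36 forms".

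Covariates are written out for the primary model only: "The model will adjust for baseline log SCr, stratification and minimisation factors (age, sex, baseline CKD stage and presence of tissue loss". For secondary outcomes the nearest statement is "Secondary outcomes will be analysed on a complete case population and reported similarly to the primary outcome using appropriate methodology to compare randomised groups".

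**The concern.** The protocol commits to a data-dependent choice of method, so this is more than a detail left open for the SAP. Three things follow.

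- **The trigger is the wrong one.** Linear regression needs a roughly normal sampling distribution for the treatment coefficient and a valid standard error. At about 78 per arm, robust or bootstrap standard errors supply that for skewed or bounded outcomes.
- **The switch changes the question.** Linear regression estimates a difference in means. A rank test compares the ordering of the two samples. Which one is reported would be settled after the data are seen, in a trial without blinding.
- **Neither branch matches the stated aim.** The contrast target is a percentage. A plain rank test yields a p-value, and linear regression on mL yields a difference in mL. For quality of life, a two-sample rank test on day-90 scores cannot use the baseline scores, and the linear branch does not say that it will.

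At stake is whether the key secondary question, how much contrast is saved, is answered by an estimate with an interval fixed in advance.

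**Working it through.** **1. The plan's own sample size, to see whether it is touched.** Inputs from Sample size calculation: SD 0.25, correlation 0.67, difference 0.075, power 90%, alpha 0.05 (taken as two-sided). With one baseline and three follow-up values, the variance factor is (1 + 2 × 0.67)/3 − 0.67² = 0.780 − 0.449 = 0.331. The effective SD is 0.25 × √0.331 = 0.144. Then n = 2 × (3.2415 × 0.144/0.075)² ≈ 77.3, so 78 per group and 156 in all. 156/0.9 = 173.3, so 174. The stated figures reproduce exactly, and nothing in this point alters them.

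**2. The contrast target.** 20% of 70 mL is 14 mL, a ratio of 0.80. No SD is given, so the power claim cannot be reproduced. The largest SD compatible with 90% power at 78 per group follows from k = 3.2415 × √(2/78) = 0.519:

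- on the mL scale, 14/0.519 ≈ 27 mL;
- on the log scale, 0.2231/0.519 ≈ 0.43, where 0.2231 = −ln 0.80.

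Power over a range of assumed SDs, 78 per group, no covariates:

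| SD in mL | Power | SD of log volume | Power |
|---|---|---|---|
| 20 | 99% | 0.30 | 99.6% |
| 27 | 90% | 0.43 | 90% |
| 30 | 83% | 0.50 | 80% |
| 40 | 59% | 0.60 | 64% |
| 50 | 42% | 0.80 | 41% |

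**3. What each method returns for the same truth.** Simulation of 3,000 trials, 78 per group, log-normal volumes without zeros, control median 70 mL, true ratio 0.80 (median difference −14 mL), covariates assumed to explain 20% of the log variance:

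| Method | Power, log SD 0.43 | Power, log SD 0.60 | Mean estimate (log SD 0.43; 0.60) |
|---|---|---|---|
| Mann-Whitney test | 87% | 63% | none from the test itself |
| Adjusted regression, mL | 92% | 65% | −15.2; −16.8 mL |
| Adjusted regression, log mL | 95% | 73% | ratio 0.80; 0.80 |

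A Hodges-Lehmann shift, if added to the rank test, averaged −13.2 mL in both settings. Only the ratio scale returns the target directly.

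The rank test falls 7 to 11 points below the adjusted log model. Most of that comes from adjustment: the unadjusted log comparison in step 2 has 90% and 64%, only about 2 to 3 points above the rank test.

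**4. Quality of life.** Adjusting for a baseline score with correlation r removes r² of the variance, worth 1/(1 − r²) − 1 in extra participants. At r = 0.5 this is 25% of the variance and 1/0.75 − 1 = 33%. At r = 0.67 it is 45% and 1/0.551 − 1 = 81%. Both correlations are assumptions. The article gives 0.67 for creatinine and nothing for EQ-5D-5L or SF-36.

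**5. The adjustment set.** Assignment of interventions and randomisation lists CKD stage, age, diabetes and tissue loss. Both analysis sections list age, sex, CKD stage and tissue loss. Diabetes is missing from one list and sex from the other.

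**The case against.** The strongest reply is that a journal article defers detail to a SAP, and that the normality criterion, the named method and the effect measure normally belong there. That stands for those details. It does not cover the rule itself, which the article states twice and which a SAP that follows the protocol would inherit.

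Four stronger readings are tempting, and the article does not support them.

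- **That the fallback drops planned covariate adjustment.** Adjustment is written only for the primary model. For secondary outcomes it is at most hinted at by the remark on similar reporting. A plain rank test would preclude adjustment, but the linear branch does not promise it.
- **That the fallback gives no estimate at all.** This is true of a bare rank test. The word *methods* in Data analysis could include quantile regression or a Hodges-Lehmann shift with an interval. Linear regression on mL would not give a percentage either.
- **That volumes in the CO2 arm will pile up at zero, so the fallback is certain.** The Interventions section says that participants in this arm "will be allowed the administration of standard iodine-based intra-arterial contrast if deemed necessary by the operators" but gives no expected volume. A planned 20% reduction leaves about 56 mL (70 − 14), which does not suggest a mass at zero. Skew is plausible because the control figure is a median, and zeros are possible.
- **That the switch costs 33% to 81% of the quality-of-life sample.** Those figures compare adjusted with unadjusted analysis, not the two branches as written.

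**Conclusion.** The point holds in this form: the article makes the analysis of the key secondary outcome and of quality of life depend on an undefined look at the data, uses a criterion that linear regression does not need, and ties neither branch to the 20% target or to the baseline scores collected.

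The weight is minor to moderate. The primary analysis and the 156/174 sample size are unaffected. For contrast volume the main loss is a fixed estimate with an interval. The loss of power is secondary and depends on assumed SDs, log-normal volumes and covariates explaining 20% of log variance. For quality of life the gain available from baseline adjustment is 25% of the variance if r = 0.5, and it scales with r². It is forgone in either branch unless adjustment is stated.

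**What to change.** Reconcile the minimisation factors first, so that the adjustment set is the one used at allocation plus any further covariate named on purpose. Then:

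- **Remove the normality trigger** from both sections.
- **Contrast volume:** prespecify one adjusted analysis that accepts zeros and reports the reduction with a 95% CI. One option is a log-link model for the ratio of mean volumes with robust standard errors. Another is quantile regression at the median, which fits a target anchored to a median of 70 mL. Choose one before any outcome data are seen.
- **EQ-5D-5L and SF-36 at 90 days:** linear regression adjusted for the same score at baseline and the minimisation factors, with robust or bootstrap standard errors.
- **Rank tests:** keep as sensitivity analyses.

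The cost is wording in the protocol and SAP before database lock, with no new data. A ratio of means is more sensitive to a few very large volumes, which the rank-test sensitivity analysis would help to expose. Quantile regression avoids that, but is uninformative at the median if more than half of an arm has zero volume.
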